## Abstract

**Introduction:**

Sepsis is a life-threatening immune disorder resulting from an dysregulated host response to infection. Adjuvant therapy is a valuable complement to sepsis treatment. Lipoic acid has shown potential in attenuating sepsis-induced immune dysfunction and organ injury in vivo and in vitro studies. However, clinical evidence of lipoic acid injection in sepsis treatment is lacking. Hence, we devised a randomised controlled trial to evaluate the efficacy and safety of lipoic acid injection in improving the prognosis of sepsis or septic shock patients.

**Methods and analysis:**

A total of 352 sepsis patients are planned to be recruited from intensive care units (ICUs) at eight tertiary hospitals in China for this trial. Eligible participants will undergo randomisation in a 1:1 ratio, allocating them to either the control group or the experimental group. Both groups received routine care, with the experimental group also receiving lipoic acid injection and the control group receiving placebo. The primary efficacy endpoint is 28-day all-cause mortality. The secondary efficacy endpoints are as follows: ICU and hospital mortality, ICU and hospital stay, new acute kidney injury in ICU, demand and duration of life support, Sequential Organ Failure Assessment (SOFA)/Acute Physiology and Chronic Health Evaluation II (APACHE II) and changes from baseline (ΔSOFA/ΔApache II), arterial blood lactate (LAC) and changes from baseline (ΔLAC), blood procalcitonin, high-sensitivity C-reactive protein, interleukin-2 (IL-2), IL-4, IL-6, IL-10, tumour necrosis factor-α (TNF-α) and interferon-γ (IFN-γ) and changes from baseline on day 1 (D1), D3, D5 and D7. Clinical safety will be assessed through analysis of adverse events.

**Ethics and dissemination:**

The study was approved by the Ethics Committee of Maoming People’s Hospital (approval no. PJ2020MI-019-01). Informed consent will be obtained from the participants or representatives. The findings will be disseminated through academic conferences or journal publications.

**Trial registration:**

ChiCTR2000039023.

Strengths and limitations of this studyThe trial utilises a randomised controlled design with a substantial sample size.The trial design mitigates the influence of confounding factors, such as terminal diseases.Adequate evidence from animal and human research supports the hypothesis that lipoic acid could protect organs against sepsis injury.This trial follows a single-blind study design rather than a double-blind design.

## Introduction

Sepsis, characterised by acute organ dysfunction resulting from a dysregulated host response to infection, is a multifaceted disorder that poses a significant mortality risk among patients in non-coronary intensive care units (ICUs).^1–3^ Despite the advancements in sepsis management over the past decade, the mortality rate still exceeds 30%, reaching up to 60% in cases of septic shock.^4^ In high-income countries, the population incidence rate of sepsis was 437 cases per 100 000 person-years, resulting in approximately 2.8 million deaths attributed to sepsis annually.^5^ Jiang *et al*^6^ reported a standardised sepsis incidence and mortality rate of 461 and 79 cases per 100 000 person-years, respectively, in China. The incidence is expected to rise further due to the ageing Chinese population, leading to an increased financial burden associated with treatment. Consequently, prioritising the management of sepsis and septic shock becomes crucial for ensuring patient safety.

The primary treatment approach for sepsis emphasises timely intervention, which includes removing the source of infection, administering appropriate antibiotics and restoring tissue perfusion through fluid resuscitation and vasoactive drugs.^7–9^ Indeed, sepsis is a syndrome rather than a specific disease, which highlights the importance of implementing adjuvant therapies that target its underlying pathophysiological mechanisms beyond primary treatment. The 2021 guidelines only provide weak recommendations for adjuvant therapies in sepsis management,^10^ such as the use of intravenous corticosteroids. Consequently, there is a pressing need for safe, effective and affordable adjuvant treatments with minimal adverse effects.

The exact mechanisms of sepsis-induced cell injury and organ dysfunction are not fully understood. However, it is widely recognised that simultaneous imbalanced activation of proinflammatory response (leading to cellular and tissue damage) and anti-inflammatory response (leading to immune system impairment) are associated with sepsis.^11–13^ Moreover, sepsis progression has been linked to the imbalance between reactive oxygen species (ROS) and antioxidant enzymes. One compound that has shown unique antioxidant properties is lipoic acid (LA), also known as 1,2-dithiolane-3-pentanoic acid. LA is a naturally occurring dithiol compound that is enzymatically synthesised in the mitochondria from octanoic acid. LA chelates several metal ions^14^ and scavenges ROS and reactive nitrogen species (RNS) both in vitro and in vivo.^15^ These actions enable LA to regenerate antioxidant molecules like glutathione, vitamin C and vitamin E.^16^ Remarkably, due to its small chemical structure, LA exhibits solubility in both water and lipids. This unique characteristic enables LA to efficiently access and permeate throughout the entire body, facilitating its favourable effects.

In a study conducted by Zhang *et al*,^17^ it was demonstrated that LA effectively attenuates lipopolysaccharide (LPS)-induced acute inflammatory responses both in vitro and in vivo. This attenuation is achieved through the activation of the phosphoinositide 3-kinase (PI3K)/protein kinase B (Akt) signalling pathway. Multiple studies^18–21^ have demonstrated that LA possesses anti-inflammatory properties and can effectively reduce LPS-induced inflammation. LA achieves this by inhibiting the activation of the nuclear factor κB (NF-κB) signalling pathway and suppressing the excessive production of proinflammatory factors. These actions contribute to the attenuation of sepsis-induced inflammation and oxidative damage in organs, highlighting the potential of LA as a therapeutic intervention for sepsis. Furthermore, LA has shown significant benefits in improving diabetic neurovascular and metabolic abnormalities.^22^ Additionally, it has been implicated in cardiovascular protection and exerting anti-inflammatory effects.^23–26^ This suggests that LA may have broad therapeutic applications beyond sepsis treatment. Considering its anti-oxidative properties, LA holds promise as a potential adjuvant for sepsis treatment. Its ability to protect tissues from oxidative stress and prevent sepsis-induced organ dysfunction makes it a candidate worth exploring further.

Indeed, LA has been investigated in various therapeutic contexts, including weight management,^27 28^ multiple sclerosis,^29^ male fertility^30^ and type 2 diabetes,^31 32^ showing promising results. However, when it comes to sepsis-induced organ dysfunction, most studies have primarily focused on animal models, particularly rats.^17 33 34^ As of today, there is a lack of human studies exploring the therapeutic effects of LA in sepsis treatment.

To address this gap in knowledge, we have designed a multicentre, single-blinded, randomised controlled trial (RCT) in China. The objective of this trial is to assess the efficacy and safety of LA injection compared with a placebo in patients diagnosed with sepsis or septic shock in ICUs. We aim to investigate the preventive and therapeutic effects of LA on suppressing inflammation, attenuating organ dysfunction, shortening ICU or hospital stay and improving patient outcomes, including mortality. By conducting this RCT, we hope to provide valuable insights into the potential benefits of LA in sepsis treatment.

## Methods and analysis

### Study design and setting

The ALIS (‘Adjuvant Lipoic acid Injection in Sepsis treatment in China’) study is a multicentre, single-blind, randomised, placebo-controlled clinical trial conducted in tertiary hospitals in China. The protocol and informed consent forms are required to undergo a thorough review and approval by the applicable ethical committees (ECs) to ensure compliance with scientific standards and human subject protection regulations at each participating centre. The study involves various departments, including general ICU, neurological ICU, surgical ICU and emergency ICU. Detailed information about the intended participating centres can be found in table 1. The enrolment period for this study is estimated to be 2 years, and the trial will conclude with the last follow-up. The study has been registered,^35^ ensuring transparency and accessibility of the study information. The study design and protocol adhere to the Standard Protocol Items: Recommendations for Interventional Trials reporting guidelines.^36^

**Table 1 T1:** Research settings and names of each ethics committee

Research setting	Ethics committee name	Hospital rank and location
Maoming People’s Hospital	Medical Ethics Committee of Maoming People’s Hospital	Tertiary, Maoming, Guangdong, China
Guangdong Provincial People’s Hospital	Medical Ethics Committee of Guangdong Provincial People’s Hospital	Tertiary, Guangzhou, Guangdong, China
Affiliated Hospital of Guangdong Medical university	Medical Ethics Committee of Affiliated Hospital of Guangdong medical university	Tertiary, Zhanjiang, Guangdong, China
Central People’s Hospital of Zhanjiang	Medical Ethics Committee of Central People’s Hospital of Zhanjiang	Tertiary, Zhanjiang, Guangdong, China
Huizhou Central Hospital	Medical Ethics Committee of Huizhou Central Hospital	Tertiary, Huizhou, Guangdong, China
Xiaolan People’s Hospital of Zhongshan City	Medical Ethics Committee of Xiaolan People’s Hospital of Zhongshan	Tertiary, Zhongshan, Guangdong, China
Third People’s Hospital of Huizhou	Medical Ethics Committee of the Third People’s Hospital of Huizhou	Tertiary, Huizhou, Guangdong, China
Yunfu People’s Hospital	Medical Ethics Committee of Yunfu People’s Hospital	Tertiary, Yunfu, Guangdong, China

### Protocol amendments

Protocol amendments will be recorded, including a concise description of the modification and a reference (date and number), in cases where changes to the existing protocol have a significant impact on subject safety, study scope or scientific quality. The coordinating investigator has a responsibility to inform all investigators, the reviewing EC and other relevant parties about these protocol amendments as required.

### Eligibility criteria

All trial centres will adhere to the same participant inclusion criteria. The inclusion criteria are as follow:

Meeting the diagnostic criteria for sepsis and septic shock, as established by the American Critical Care Medical Association/European Critical Care Medical Association (Sepsis-3 criteria).^37^Age between 18 and 80 years.Within 48 hours of receiving a diagnosis of sepsis or septic shock.Having provided signed informed consent.

The exclusion criteria for participant selection are as follows:

Female patients who are pregnant or lactating.Presence of persistent infection sources that cannot be effectively eliminated through procedures such as puncture, drainage, debridement, or other surgical operations.Participation in another clinical trial.Current treatment with other medications that have antioxidant effects, such as vitamin C and vitamin E.Accompanied by non-infectious but life-threatening conditions, such as advanced tumour, severe craniocerebral injury, uncontrollable massive bleeding, cardiogenic shock, etc.Lack of approval for comprehensive and active life support treatment.Allergy to LA or similar active agents (eg, vitamin B), or previous intolerance to the recommended dose of LA.

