### Interventions

The participants will be randomly assigned to either the placebo group or the LA group and treated according to their assigned treatment plan. In the placebo group, patients will receive a placebo consisting of 250 mL of normal saline. In the treatment group, patients will receive a solution containing an LA injection of 600 mg (provided by Yabao Pharmaceutical Group Co.) dissolved in 250 mL of normal saline. To prevent exposure to light, both the LA and the placebo solutions will be wrapped in aluminium platinum paper. It is important that the intravenous drip time does not fall short of 30 min. Concomitant care include standard sepsis bundle treatment and other routine care. The critical care physicians are encouraged to adhere to the updated Surviving Sepsis Campaign guidelines,^7^ although the final decision is at the discretion of the physicians as per institutional guidelines. The number and percentage of patients in both the treatment and placebo groups who deviated from the sepsis bundle treatment will be documented.

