This study design possesses several strengths. First, the utilisation of a large sample size in this RCT can enhance our understanding of the efficacy of LA, a commonly used adjuvant drug in sepsis treatment lacking evidence-based support. Second, the exclusion of terminal disease as a confounding factor is addressed in this study. Sepsis can occur in patients already succumbing to other causes (eg, terminal cancer), and inherent mortality associated with sepsis is a characteristic of the syndrome itself. Third, the hypothesis that LA provides organ protection against sepsis injury is backed by substantial evidence from both animal and human research. Nonetheless, there are certain limitations that should be acknowledged. First, the relatively limited number of participating centres may introduce selection bias, potentially affecting the generalisability of the research findings to other contexts or settings. Second, this study design adopts a single-blind approach, which could introduce diagnostic bias by the investigators, potentially resulting in treatment imbalances between the control and treatment groups.

In conclusion, the ALIS study is a large-sample-sized, multicentre, single-blinded, randomised, parallel-group, placebo-controlled trial in China. It is designed based on robust evidence from basic and clinical studies. The anticipated outcomes of this trial have the potential to offer evidence-based recommendations for sepsis prevention in critically ill patients.

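### As worded, the antioxidant exclusion bars only antioxidants other than lipoic acid, so a patient already receiving lipoic acid can be randomised, possibly to saline

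*Protocol article*

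**What the plan says.** Two exclusion criteria in the protocol article (Eligibility criteria) bear on the point.

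- The antioxidant criterion: "Current treatment with other medications that have antioxidant effects, such as vitamin C and vitamin E".
- The only criterion that names LA: "Allergy to LA or similar active agents (eg, vitamin B), or previous intolerance to the recommended dose of LA".

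The entry window in the same section is "Within 48 hours of receiving a diagnosis of sepsis or septic shock".

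On background use, the Discussion refers to "LA, a commonly used adjuvant drug in sepsis treatment lacking evidence-based support".

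On care alongside study treatment, the Interventions section states: "Concomitant care include standard sepsis bundle treatment and other routine care". Physicians are encouraged to follow the sepsis guidelines, but "the final decision is at the discretion of the physicians as per institutional guidelines". The section also plans to count the patients in each arm "who deviated from the sepsis bundle treatment will be documented".

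**The concern.** The sponsor evidently regarded background antioxidant treatment as a confounder that deserved an exclusion. The wording chosen catches vitamins C and E but not the most direct confounder, the test drug given outside the trial. The criterion that does name LA foresees earlier exposure, yet it removes only patients who did not tolerate it.

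Two things are at stake.

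- **Baselines.** SOFA, APACHE II, lactate, procalcitonin, hs-CRP and the cytokines are all to be analysed as changes from baseline. In a patient already on LA, the baseline is not an untreated value, whichever arm the patient joins.
- **Contrast.** If LA begun before entry continues in a patient allocated to saline, that patient is not an untreated control. If LA works, the difference in 28-day mortality shrinks. An intention-to-treat analysis keeps the randomisation intact but does not restore the lost difference.

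**Working it through.** **Step 1: the text.** Take a patient 36 hours after diagnosis whose ICU team has already started LA, and who tolerates it. Apart from LA use the patient meets all criteria.

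| Criterion | Does it exclude this patient? |
|---|---|
| Within 48 hours of diagnosis | No: 36 hours is inside the window |
| Other antioxidant medications | No: LA is the drug that *other* is measured against |
| Allergy to, or previous intolerance of, LA | No: the drug is tolerated |
| Remaining exclusions (pregnancy or lactation, uncontrolled source, another trial, other life-threatening conditions, no approval for full life support) | No: none concerns LA |

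The patient is eligible. Replace LA with vitamin C and the patient is excluded. The reading follows from the printed criteria and needs no assumption about what the full protocol contains.

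**Step 2: the plan's own sample size.** Inputs from the Sample size section: control mortality p1 = 0.382, LA mortality p2 = 0.229, one-sided alpha 0.025, power 80%, 160 per arm before dropout. With the pooled-variance formula

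n = [z(0.975)·√(2·p̄·(1−p̄)) + z(0.80)·√(p1(1−p1) + p2(1−p2))]² / (p1 − p2)²,

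and p̄ = (0.382 + 0.229)/2 = 0.3055, the two roots are 0.6514 and 0.6424. Then n = [(1.960 × 0.6514 + 0.8416 × 0.6424) / 0.153]² ≈ 141.1, so 142 per arm. With a continuity correction it is 154. Neither equals 160. At the stated rates, 160 per arm gives

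power = Φ{[0.153·√160 − 1.960 × 0.6514] / 0.6424} = Φ(1.025) ≈ 84.7%.

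This mismatch is a separate matter. It is noted here only because 84.7%, not 80%, is the correct starting point for the illustration.

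**Step 3: illustration of dilution.** The documents give no rate of non-study LA use. Assume that a share c of the control arm receives LA and gets the full planned benefit, with the LA arm unchanged. The control rate becomes

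p1(c) = 0.382 − c × (0.382 − 0.229) = 0.382 − 0.153c.

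| c (assumed) | Control rate | Difference (points) | Power at 160 per arm | n per arm for 80% power, before dropout |
|---|---|---|---|---|
| 0 | 38.2% | 15.3 | 84.7% | 142 |
| 5% | 37.4% | 14.5 | 81.2% | 156 |
| 10% | 36.7% | 13.8 | 77.1% | 172 |
| 20% | 35.1% | 12.2 | 67.6% | 215 |
| 30% | 33.6% | 10.7 | 56.7% | 277 |

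For c = 10%: control rate 0.3667, difference 0.1377, roots 0.6467 and 0.6394, so power = Φ{[0.1377·√160 − 1.960 × 0.6467] / 0.6394} = Φ(0.742) ≈ 77.1%.

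Only the product of the share exposed and the fraction of effect they obtain enters the formula. If 10% of controls obtained half the effect, the 5% row would apply (81.2%). The table is therefore an upper bound on the loss at each rate.

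**The case against.** **The criterion's purpose covers LA.** The Introduction describes LA as an antioxidant, and *other* may have been meant as other than the study infusion. That may well be the intent. But eight centres screen from the text, and the text does not say it. The objection makes this a drafting defect; it does not remove it.

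**A condensed article proves little by silence.** This stands for the period after randomisation. Reading the routine-care wording, a reader might infer that controls are free to receive LA or vitamin C once randomised. The article does not say so: the discretion clause concerns adherence to sepsis guidelines, and a list of prohibited medication may sit in the full protocol. Nor does the article show that non-study LA goes unrecorded, because the case report form is not shown. The entry criteria are different, since the article prints them as a list.

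**Evidence of background use is thin.** Also true. The Discussion's remark carries no figure and no reference. A reader might add diabetic patients on LA, from the Introduction's statement that "LA has shown significant benefits in improving diabetic neurovascular and metabolic abnormalities". That reports research findings; it does not say that patients in this population take the drug.

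**Differential bias.** Because the Discussion concedes that single-blinding could lead to treatment imbalance, a reader might infer that physicians would give antioxidants mainly to controls. The caveat is general and does not mention antioxidants, and both solutions are wrapped. The documents do not support the inference.

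**Randomisation balances prior exposure, and a per-protocol analysis is planned.** LA that stops at entry is balanced between arms in expectation, so dilution requires that it continue; the baseline problem remains. The per-protocol set requires patients to meet the eligibility criteria, which an LA user does as they are worded, and it gives up part of the randomised comparison.

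**Conclusion.** The concern holds for entry to the trial. The printed exclusion leaves a patient already receiving LA eligible within 48 hours of diagnosis, while refusing a user of vitamin C or E. The protocol's own description of LA as common in sepsis care makes such patients foreseeable, though not shown to exist.

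The consequence is LA-exposed baselines in both arms and, where LA continues in patients allocated to saline, a smaller contrast. With 10% of controls assumed to receive LA at full effect, power at 160 per arm falls from about 85% to about 77%, below the planned 80%. With 5% it stays just above, at about 81%. The rates are assumptions and the full-effect model is the least favourable case.

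On treatment after randomisation, the conclusion is limited: the concomitant-care text and the exclusion do not say whether the restriction continues, and they need to be reconciled. The documents establish neither that controls are given LA nor that any imbalance favours one arm.

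**What to change.** 1. Reword the exclusion so that it covers current or recent treatment with non-study lipoic acid as well as other medications with antioxidant effects. The sponsor sets the look-back period.
2. Reconcile the Interventions text on routine care with the exclusion by stating whether the restriction on non-study LA and other antioxidants continues during study treatment. Which rule to adopt is for the investigators.
3. Report non-study LA by arm, before and after randomisation, including for patients already enrolled. If the case report form already captures it, this needs only a table.

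Cost: a few patients on LA become ineligible. The change is short, but recruitment began on 26 August 2021. Under the Protocol amendments section, an amendment has to be recorded and notified to all investigators and the reviewing ethics committee, with eight centres involved. Patients enrolled before the change cannot be re-screened, so for them the report by arm is the only safeguard.

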### Interventions

The participants will be randomly assigned to either the placebo group or the LA group and treated according to their assigned treatment plan. In the placebo group, patients will receive a placebo consisting of 250 mL of normal saline. In the treatment group, patients will receive a solution containing an LA injection of 600 mg (provided by Yabao Pharmaceutical Group Co.) dissolved in 250 mL of normal saline. To prevent exposure to light, both the LA and the placebo solutions will be wrapped in aluminium platinum paper. It is important that the intravenous drip time does not fall short of 30 min. Concomitant care include standard sepsis bundle treatment and other routine care. The critical care physicians are encouraged to adhere to the updated Surviving Sepsis Campaign guidelines,^7^ although the final decision is at the discretion of the physicians as per institutional guidelines. The number and percentage of patients in both the treatment and placebo groups who deviated from the sepsis bundle treatment will be documented.

